### 2.3. Eligibility criteria

#### 2.3.1. Inclusion criteria.

Adults aged 19 years or over but under 65 years.Eligible subjects through screening tests and whose lipid profile results after 4 weeks of lifestyle modification correspond to 1 or more of the following: (a) TC ≥ 200 mg/dL, (b) TG 150 to 499 mg/dL, (c) LDL-cholesterol 130 to 250 mg/dL, and (d) HDL-cholesterol < 40 mg/dL (However, even if the subject corresponds to more than 1, LDL-cholesterol should not exceed 250 mg/dL, and TG should not exceed 499 mg/dL).Voluntary signed written informed consent after sufficient explanation of this study.

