### 2.8. Sample size calculation

This is a preliminary exploratory study to assess the clinical effect and safety of GBH on serum lipid levels and CV risk in patients with borderline hyperlipidemia. According to a study that recommended the minimum sample size for the preliminary study,^[25]^ the minimum effect size was assumed to be 0.20, a dropout rate of 20% was considered, and a total of 90 participants (45 in each group) are set as the target sample size.

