### 2.12. Statistical analysis

An independent statistician will conduct statistical analysis using SAS® Version 9.4 (SAS Institute Inc., Cary, NC). According to principle, an efficacy analysis will be conducted using a full analysis set according to the intention-to-treatment principle, including all randomly assigned participants who received at least 1 evaluation after the investigational product has been prescribed at least once. If necessary, per-protocol set analysis will also be conducted, including only participants who have completed the entire process as described in the protocol and have no significant violations. Participants with < 70% compliance with the investigational product will be excluded from the per-protocol set analysis. The safety analysis will include all data obtained from participants who have taken at least 1 investigational product.

The demographic and general clinical characteristics of the participants will be summarized by grouping. Continuous data will be presented as mean and 95% confidence intervals or medians according to the data distribution, and dichotomous data as frequency and percentage. Continuous data will be analyzed using the independent t-test or Wilcoxon rank-sum test, and dichotomous data will be analyzed using the chi-square test or Fisher exact test.

The primary outcome of this study is the mean change in LDL-C levels from baseline to week 8. A 2-sided test with a significance level of 5% will be performed using an analysis of covariance with baseline as the covariate and the treatment group as the fixed factors. The intragroup changes in outcome measures from baseline to posttreatment will be analyzed using the paired *t* test or Wilcoxon signed-rank test for continuous variables and the chi-square test or Fisher exact test for dichotomous variables. Furthermore, repeated-measures analysis of variance will be used to compare the differences in trends between visits in each group. Missing values will be replaced with the multiple imputation method. If necessary, subgroup analysis can be performed by categorizing the initial characteristics of participants at the screening or baseline visit.

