## 4. Discussion

This is a study protocol for a randomized, double-blind, placebo-controlled, parallel, investigator-initiated pilot clinical trial evaluating the effect of GBH on patients with borderline hyperlipidemia. We will evaluate the preliminary efficacy and safety of an 8-week administration of GBH compared with placebo granules and assess the feasibility of large-scale randomized controlled trials (RCTs). To the best of our knowledge, this is the first RCT to assess the effect of GBH in patients with hyperlipidemia.

GBH is 1 of the most frequently prescribed herbal medicines for patients with impaired blood circulation, known as blood stasis syndrome in Korea, China and Japan.^[27]^ The main components of GBH, such as amygdalin derived from *Persicae Semen*, paeoniflorin derived from *Paeoniae Radix*, and cinnamic acid derived from *Cinnamomi ramulas*, have antilipid, antiplatelet, antithrombosis, and antiarteriosclerosis effects.^[14]^

GBH is not approved by the ministry of food and drug safety as a medicine for dyslipidemia^[15]^ but a significant number of preclinical and clinical studies have been reported that have identified the blood lipid-lowering effects of GBH.^[16–21]^

If the treatment effect and safety of GBH compared to placebo granules are found to be promising in this study and the study design is feasible, we will design a confirmatory, large-scale RCT based on the results of the study to draw definitive conclusions regarding the efficacy of GBH.

In conclusion, this article presents a protocol for a rigorously well-designed, double-blind, placebo-controlled pilot RCT of GBH in patients with hyperlipidemia. The strengths of our study include using placebo granules as the control and using the objective blood lipid parameter, LDL-C, as the primary outcome to minimize performance bias and detection bias. The findings of this study are expected to provide a basis for large-scale, confirmatory RCT to confirm the efficacy and safety of GBH in treating patients with hyperlipidemia. Additionally, stronger evidence for GBH as a treatment option for hyperlipidemia may be provided to clinicians, patients, and researchers.

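### The optional subgroup analysis would categorise initial characteristics and leaves the source visit open; for continuous characteristics, an interaction term using the last pre-dose value would use the data better

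*Protocol article*

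**What the plan says.** Subgroups get one sentence, at the end of section 2.12, which applies only if needed: "subgroup analysis can be performed by categorizing the initial characteristics of participants at the screening or baseline visit". It names no characteristic, cut point, number of groups or test. The primary comparison in the same section is described as follows: "A 2-sided test with a significance level of 5% will be performed using an analysis of covariance with baseline as the covariate", with treatment group as the fixed factor.

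Section 2.3.1 admits participants whose lipid results after the lifestyle period "correspond to 1 or more of the following", the list being TC, TG, LDL-C and HDL-C. Section 2.8 gives the size: "a total of 90 participants (45 in each group) are set as the target sample size", and "a dropout rate of 20% was considered".

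Table 1 (section 2.1) shows what is measured when. Demographics and medical history are taken at the first screening only. Laboratory tests are marked at both screening visits and, as the table was read, not in the baseline column. The blood stasis questionnaire is marked at the first screening and at baseline. The first screening comes before the 4-week lifestyle period.

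Section 4 says that, if the results are promising and the design feasible, "we will design a confirmatory, large-scale RCT based on the results of the study".

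**The concern.** A participant can enter on TG, TC or HDL-C with an unremarkable LDL-C, yet LDL-C is the primary outcome. Whether the effect depends on the starting value is therefore a natural question for this trial, and the answer bears on eligibility for the confirmatory trial.

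The stated method serves that question poorly in two ways.

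- **Categorising.** Cutting a continuous variable treats everyone on one side of the cut as alike and discards the variation within each group. Categories also invite a separate test in each, and such tests do not show whether the effect differs between them.
- **Visit.** For lipids and the blood stasis score, the wording allows a value from before or from after the lifestyle period. The same participant could fall into different categories depending on that choice. For age or sex the choice makes no practical difference.

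At stake is a misleading lead, or a missed one, handed to the next trial. The primary analysis is unaffected.

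**Working it through.** The plan gives no figure for subgroup analysis, so there is none to reproduce.

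**Inputs.** 45 per arm and 20% dropout (section 2.8) give 45 × 0.80 = 36 evaluable per arm, 72 in all. Two-sided alpha is 0.05 (section 2.12, stated for the primary test and assumed for subgroups). The effect size of 0.20 in section 2.8 is read as a standardised difference, which the text does not say. Median splits, larger effects, interaction slopes and between-visit correlations are assumptions.

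**1. Information kept by a cut.** For a normal characteristic with a linear effect, a cut at proportion p keeps φ(z_p)² / [p(1−p)].

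- Median split: 0.3989² / 0.25 = 0.637 = 2/π, so 36.3% is lost. Of 72 participants, 72 × 0.637 ≈ 46 are left in effective terms.
- Cut at the 25th percentile: 46.1% lost.
- Tertiles: 20.7% lost. Quartiles: 13.9% lost.
- Median split of a uniform variable: 25% lost. Of a lognormal variable (sigma 0.5): about 48% lost.
- A factor already categorical, such as sex: nothing lost.

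**2. Power of the interaction test.** Simulated at 36 per arm with standard normal residuals. The slope is the change in treatment effect, in SD, per SD of the characteristic.

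| Assumed slope | Continuous | Median split |
|---|---|---|
| 0.2 | 13% | 10% |
| 0.5 | 52% | 36% |
| 0.6 | 68% | 48% |
| 0.7 | 80% | 59% |

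With no interaction, both forms reject in about 5% of trials.

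**3. Reading two halves separately when the effect is the same in both.** Each half has about 18 per arm, so the noncentrality is d × √(18/2) = 3d with 34 degrees of freedom. If P is the power in one half, the chance that exactly one half is significant is 2P(1−P).

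- d = 0.20: P = 0.090, giving 2 × 0.090 × 0.910 ≈ 16%.
- d = 0.50: P = 0.308, giving 2 × 0.308 × 0.692 ≈ 43%. Simulation gives 42%.
- d = 0.67: P = 0.497, giving 50%, the maximum of 2P(1−P).
- No effect: 2 × 0.05 × 0.95 = 9.5% in either direction, and 2 × 0.025 × 0.975 ≈ 4.9% in favour of GBH.

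The standard error of the difference between halves is √(4/18) = 0.471 SD, twice the overall √(2/36) = 0.236. By chance alone the halves differ on average by 0.471 × √(2/π) = 0.38 SD.

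**4. Several characteristics, no effect.** With five independent characteristics split at the median, simulation gives at least one significant half in about 29% to 30% of trials. Five continuous interaction tests give at least one false positive in about 1 − 0.95⁵ = 22.6%.

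**5. Choice of visit.** If two pre-treatment values are bivariate normal with correlation ρ, the share changing side of the median is arccos(ρ)/π: 25.3% at ρ = 0.7 and 20.5% at ρ = 0.8. The documents give no correlation.

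**The case against.** The strongest reply is that section 2.12 states neither a median split nor a test within each half. Forming categories does not rule out a treatment-by-category interaction, and factors, cut points and tests are commonly settled in the analysis plan, which is not shown. This stands. The figures above are consequences of assumed ways of carrying out the sentence, and the absence of a subgroup list is no finding. What remains is that categorising is the one method named, and a better one is available in the model already planned.

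A reader might infer that the plan will discard a third of the information and will make half the trial look like responders. The documents do not support that. The analysis is conditional, the loss depends on the variable and the cut, and the article makes no responder claim. At the protocol's own 0.20, the one-sided-looking pattern arises in about 16% of trials.

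A reader might also expect the fix to remove chance findings. It does not: over five characteristics it lowers them only from about 29–30% to about 23%, and an interaction test on categories errs equally often. The gain is mainly in power, and the slopes of 0.5 to 0.7 at which it shows clearly are large.

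On the visit, the wording may only reflect where each characteristic is recorded. That is a fair reading for demographics and medical history. It does not settle the matter for lipids, which have two screening values, or for the blood stasis score, which has a screening and a baseline value.

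Finally, the trial is exploratory and a confirmatory trial is meant to follow. That limits the weight of the point, although these results are meant to shape that trial.

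**Conclusion.** The point holds as a minor improvement to the stated method. For continuous characteristics, categorising costs about 36% of the information on effect modification with a median split and 21% with tertiles, given a roughly normal variable and a linear effect. The range runs from nothing for a factor such as sex to about 48% for a median split of a skewed variable. In power terms, a slope of 0.5 SD per SD would be detected in 52% of trials with the variable kept continuous, against 36% with a median split, at 36 per arm.

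The risk that a uniform effect looks confined to one subgroup, about 16% at 0.2 SD and 42% at 0.5 SD, applies only if subgroup p-values are read separately after a median split. The visit ambiguity is real only for variables measured more than once before treatment. Neither issue touches the primary analysis.

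**What to change.** Replace the subgroup sentence in section 2.12 with text to this effect:

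- Effect modification will be examined by adding a treatment-by-characteristic interaction to the ANCOVA, with continuous characteristics kept continuous.
- Each characteristic measured more than once before treatment will be taken from the last measurement before the first dose, after the lifestyle period.
- Results will be given as the interaction estimate with its 95% CI and labelled exploratory.
- Categories, and factors that are categorical by nature, may be shown descriptively, without separate significance claims within subgroups.

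Baseline LDL-C is already the covariate in the ANCOVA, so for that characteristic the change is one product term. The cost is one rewritten sentence and no new data. The downside is an assumption that the effect changes linearly with the characteristic, which a plot can check. Power for interactions stays modest with about 72 evaluable participants, and multiplicity remains if several characteristics are examined, so the number examined should be reported.

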## 3. Ethics and dissemination

This trial will be performed in accordance with the Declaration of Helsinki and the Good Clinical Practice Guidelines and CONSORT Guidelines. This study was permitted by the ministry of food and drug safety on investigational new drug application on August 12, 2021 and approved by the IRB of Kyung Hee University, Seoul, Republic of Korea (KOMCIRB202110012001) on November 26, 2021. Written informed consent will be obtained from all participants prior to their enrollment in the study. The results will be published in a peer-reviewed journal and disseminated electronically and in print, regardless of the results.

## 4. Discussion

This is a study protocol for a randomized, double-blind, placebo-controlled, parallel, investigator-initiated pilot clinical trial evaluating the effect of GBH on patients with borderline hyperlipidemia. We will evaluate the preliminary efficacy and safety of an 8-week administration of GBH compared with placebo granules and assess the feasibility of large-scale randomized controlled trials (RCTs). To the best of our knowledge, this is the first RCT to assess the effect of GBH in patients with hyperlipidemia.

GBH is 1 of the most frequently prescribed herbal medicines for patients with impaired blood circulation, known as blood stasis syndrome in Korea, China and Japan.^[27]^ The main components of GBH, such as amygdalin derived from *Persicae Semen*, paeoniflorin derived from *Paeoniae Radix*, and cinnamic acid derived from *Cinnamomi ramulas*, have antilipid, antiplatelet, antithrombosis, and antiarteriosclerosis effects.^[14]^

GBH is not approved by the ministry of food and drug safety as a medicine for dyslipidemia^[15]^ but a significant number of preclinical and clinical studies have been reported that have identified the blood lipid-lowering effects of GBH.^[16–21]^

If the treatment effect and safety of GBH compared to placebo granules are found to be promising in this study and the study design is feasible, we will design a confirmatory, large-scale RCT based on the results of the study to draw definitive conclusions regarding the efficacy of GBH.

In conclusion, this article presents a protocol for a rigorously well-designed, double-blind, placebo-controlled pilot RCT of GBH in patients with hyperlipidemia. The strengths of our study include using placebo granules as the control and using the objective blood lipid parameter, LDL-C, as the primary outcome to minimize performance bias and detection bias. The findings of this study are expected to provide a basis for large-scale, confirmatory RCT to confirm the efficacy and safety of GBH in treating patients with hyperlipidemia. Additionally, stronger evidence for GBH as a treatment option for hyperlipidemia may be provided to clinicians, patients, and researchers.
